### Participant timeline (SPIRIT point 13)

Figure 1 SPIRIT Table [31] shows details on the schedule of enrolment, interventions, and assessments.

**Fig. 1 Fig1:**
[figure not shown]
Schedule of enrolment, interventions, and assessments. Template Source: Chan et al. [31]

## Outcomes (SPIRIT point 12)

Primary outcomes:Measurement of the extent of HIV- and TB-related stigma among the public healthcare workforce in the Free State Province of South Africa, and the generation of information on the sources of such stigma.(Time points: rough estimates calculated by December 2016 to inform partners’ decision on trial continuation; Year 4, December 2018, calculate the change in the extent of stigma by comparing measures obtained in baseline statistics *with* measures generated in post-intervention survey data)Evidence-based, stigma-reduction interventions are developed and tested in randomly selected public hospitals in the Free State Province of South Africa.(Time points: start of interventions in Year 3, March 2017 to Year 4, December 2018 when quantitative data from the post-intervention survey, and the qualitative data from focus groups and interviews are generated and analysed)

Secondary outcome:

The environment in which HCWs in intervention hospitals seek care is improved.By ‘environment’ we mean, for instance, that greater awareness of HIV and TB stigma—and hopefully diminished stigma—can create a workplace that is more sensitised and empathetically responsive to human rights. We also anticipate that when staff who test and treat other staff within a facility are well supported clinically, they are likely to provide more confident and accurately tailored services. In turn, this could encourage HCWs to seek and use health services provided in the workplace, which diminishes time taken off work and should help to some extent to alleviate HCW shortages and associated pressures on other HCWs.

(Time point: Year 4, December2018, when quantitative data from the post-intervention survey, and qualitative data from focus groups and interviews are generated and analysed)

## Data collection and management (SPIRIT point 18a)

Fieldworkers experienced in health research are used for all data collection stages and given additional training to sensitise them to the requisite quality and standardisation of research processes. In the case of qualitative work, fieldworkers work side-by-side with CHSR&D research team members.

Small tokens of appreciation in the form of a shopping voucher (for R50; approximately US$4) and small gifts (chocolates, pens, and wristbands branded with the imagery and slogan of the social marketing campaign) are supplied to fieldworkers and researchers to give to participants who complete the surveys, participate in focus groups/ one-on-one interviews, or attend the change-agent training.

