## Methods/design

### Trial design (SPIRIT point 8)

The research follows a stratified cluster RCT design. Pre intervention, a self-administered questionnaire with the pilot study’s validated stigma scales was used to measure stigma and other key variables among randomly selected HCWs in all eight randomly selected sites. The intervention comprises of stigma reduction activities at three social-ecology levels (individual, community, and structural) in the four intervention sites. To evaluate implementation, an outside assessor will appraise the trial mid-way through its implementation, partly by collecting qualitative data from purposively selected HCWs. Post intervention, all respondents from baseline will be followed up using the same scales with added questions on interventions. Quantitative and qualitative data will be collected to assess the size of the impact as well as to uncover the processes through which the interventions may impact on stigmatisation.

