### Social and Behavioural Change Communication (SBCC) interventions

These are the priority interventions and comprise two components: training HCW change agents, and a social marketing campaign.

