#### The second SBCC intervention is a social marketing campaign promoting stigma reduction

Targeting all levels of staff, and all spaces in the hospital, the social marketing campaign is designed around one branded slogan and one branded image. The slogan (in three languages) says: *Let us Stop stigma. Be kind to yourself. Be kind to others*. This refers back to theory and the division of stigma into *internal* stigma (be kind to yourself) and *external* stigma (be kind to others). The image is very bold: a large open hand, positioned like a stop signal, in a red *shwe-shwe* design. *Shwe-shwe* is a traditional South African printed fabric much loved by people of all races and from all walks of life.

The slogan is repeated on different sized posters displayed throughout the different hospital wards, as well as administrative and meeting spaces. There is also a range of promotional gifts (pens; chocolates, wristbands; fridge magnets) branded with the same slogan and image, which we hand out to everyone in the facility.

Social marketing materials can be very short-lived in a recipient’s memory. This is why we have the same message and the same image communicated in different media and in different spaces, and why we hand out promotional gifts throughout the hospital on more than one occasion.

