### Post-intervention data collection

The same processes and protocols are followed for the post-intervention survey. Respondents from the baseline survey are tracked down via their unique identifiers and asked to complete the post-intervention questionnaire. As noted before, there was a 50% oversampling of respondents to allow for loss-to-follow up between baseline and post-intervention surveys (SPIRIT point 18b).

To ensure comparability, the post-intervention survey will resemble the pre-intervention survey, thus including the HIV/AIDS and TB stigma scales as well as the range of other key outcome measures related to stigma at the individual, community, and structural levels—as described above. The post-intervention survey will also have a new section to measure the reach and appeal of the stigma interventions.

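### As written, the survey-token rule may put campaign-branded gifts into control hospitals; it needs a limit by arm

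*Protocol article*

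**What the plan says.** Under Trial design, the baseline questionnaire "was used to measure stigma and other key variables among randomly selected HCWs in all eight randomly selected sites", and all baseline respondents are to be followed up. The same section confines delivery of the intervention: "The intervention comprises of stigma reduction activities at three social-ecology levels (individual, community, and structural) in the four intervention sites".

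The section on SBCC interventions says of them: "These are the priority interventions and comprise two components: training HCW change agents, and a social marketing campaign". The campaign section then lists what the campaign hands out: "promotional gifts (pens; chocolates, wristbands; fridge magnets) branded with the same slogan and image, which we hand out to everyone in the facility".

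The opening text of Data collection and management, which stands above the separate baseline and post-intervention subsections, describes thank-you tokens: a R50 shopping voucher and "small gifts (chocolates, pens, and wristbands branded with the imagery and slogan of the social marketing campaign". The recipients are survey completers ("slogan of the social marketing campaign) are supplied to fieldworkers and researchers to give to participants who complete the surveys"), focus-group and interview participants, and change-agent trainees. Neither arm nor survey round is mentioned. For follow-up, the Post-intervention data collection section adds: "The same processes and protocols are followed for the post-intervention survey". It also announces a new questionnaire section on the reach and appeal of the interventions.

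**The concern.** The same three kinds of branded item appear twice: once as a means of delivering the campaign message, and once as a thank-you for answering a survey that also runs in control hospitals. Followed literally, the token rule sends one element of the intervention into sites that are meant to receive none of it.

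What is at stake is the contrast between arms. If control staff take in the slogan through these items, the estimated difference in stigma shrinks toward zero. If control respondents received such items before answering the follow-up questions on reach, their answers would partly record exposure that the study team itself created. An analysis cannot readily undo either effect, whereas the fieldwork rule is easy to change.

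**Working it through.** The document states no figure for contamination, so the main check is to set its statements side by side.

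**1. Does the rule cover control respondents?** The rule names people who complete the surveys. The surveys run in eight hospitals, four of them control. Under Sampling, 237 of the 584 required respondents are in control sites. Nothing in the article provides plain tokens there or discusses contamination from tokens. As written, the rule covers them.

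**2. Are the items intervention material?** Pens, chocolates and wristbands appear in both lists, in both cases with the campaign's slogan and image. The section on change-agent training adds that trainees receive branded wristbands and pens to support their conversations with co-workers. So the items do count as intervention material, but only as one element of it. Posters, training and clinical support do not travel with the token.

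**3. When could exposure matter?** The dates come from Trial status, the Discussion and the section on discontinuing or modifying interventions:
- February 2016: baseline recruitment begins.
- November 2016: the redesign of the interventions is completed.
- March 2017: recruitment for the first phase of interventions begins.
- June to July 2017: first training series, reported together with distribution of the first set of campaign materials.
- 2018: follow-up survey.

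The Background says that campaign imagery had been piloted before the trial. Branded items at baseline are therefore possible, but nothing shows that they were used.

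**4. What are the routes?**

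| Token given | Respondent's own follow-up answers | Colleagues' follow-up answers |
|---|---|---|
| After the follow-up questionnaire | Cannot be affected, including the reach items | Possible if colleagues not yet surveyed see the items |
| After the baseline questionnaire | Possible, because the same people are measured again | Possible |

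The follow-up route is real but narrow. Fieldworkers make at least three to four contact attempts and may collect forms later, so respondents within one hospital finish at different times.

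**5. In which direction?** Suppose baseline tokens went to both arms and their effect g simply adds to everything else. With a true intervention effect D, the contrast is (D + g) − g = D, so nothing is lost. Dilution needs the token to stand in for something that intervention staff receive later anyway; the contrast is then D − g. For colleagues who see items at follow-up this is plausible, because intervention hospitals already have the campaign. The bias is then toward no difference.

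**6. Can it be sized?** Only the plan's starting point can be reproduced. With means 0.85 and 0.65, SDs 0.71 and 0.39, two-sided 5% and 90% power:

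n = (1.960 + 1.282)² × (0.71² + 0.39²) / 0.20² = 10.507 × 0.6562 / 0.04 = 172.4, which rounds up to the stated 173 per arm before the design effect.

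If a share f of the 0.20 effect reached controls, nominal power would be Φ(0.20(1 − f)/√(0.6562/173) − 1.960):
- f = 0: 90.1%
- f = 5%: 87.0%
- f = 10%: 83.2%
- f = 20%: 73.8%

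These figures are purely illustrative. No value of f has a source in the document, and the calculation takes the planned 90% power and the design effect of 1.7 as given.

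**The case against.** The strongest reply is that delivery to controls is inferred and not stated. The token text pools a list of gifts with a list of recipients and does not say that every recipient gets every gift. The branded items may have been meant mainly for change-agent trainees, and the Trial design section confines the intervention to four sites. The full protocol is an additional file that is not shown, and an article may condense which token goes where. This stands as a reason to write that the trial *may* expose controls. It does not remove the conflict, because the only rule in view names survey completers and makes no exception.

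The timing objection also stands. A token given on completing the follow-up questionnaire cannot alter that person's answers, and the dates make branded baseline gifts uncertain.

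A reader might infer something stronger: that a large share of control staff received campaign material and that power falls well below 90%. Applying 50% oversampling to the 237 control respondents gives 237 × 1.5 / 4 = 88.9 per control hospital, or 40% of the stated average of 220 staff. That count presumes branded gifts at baseline, which is not shown. Any power loss built on it needs an invented transfer share, and it must assume that the gift replaces later exposure and does not merely add to it in both arms. The campaign section itself notes that such materials may soon be forgotten, which argues against a lasting effect from a single gift.

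A reader might also infer that the reach measure is spoiled. That too holds only if branded items were given before the follow-up questionnaire. Otherwise, exposure reported in control hospitals could help to detect contamination.

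**Conclusion.** The inconsistency is real: the token rule, as written, covers respondents in control hospitals and gives them items that the same article counts as part of a priority intervention reserved for the other arm. The likely consequence is some dilution toward no difference, of unknown and possibly small size. At follow-up it runs only through colleagues still to be surveyed. A direct effect on the measured cohort and on control reach answers depends on branded items having been given at baseline, and the document leaves that open.

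This should be fixed, but it does not by itself undermine the trial. The conclusion rests on reading the token rule as applying to all survey completers in both arms, which is its plain meaning but is nowhere confirmed.

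**What to change.** Three changes:

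- Give survey, focus-group and interview participants in control hospitals only unbranded tokens, meaning the voucher and plain gifts. Preferably do the same for all survey respondents in both arms, so that fieldwork is identical across arms.
- Keep branded items for the social marketing campaign and the change-agent training in the four intervention hospitals.
- State whether branded items were given at control sites at baseline. If they were, report how many, alongside the follow-up results on reach.

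The cost is small: plain pens and chocolates in place of branded ones, and a line in the fieldwork instructions. The analysis does not change. The article places the follow-up survey in 2018, after the point at which it was written, so the rule could still be set for that round. For baseline, only disclosure remains possible.

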### Baseline data collection

Once the fieldworkers track down the randomly selected individuals and obtain informed consent from those willing to participate (described earlier in the section ‘Participants’ sub-section ‘Recruitment’) (*SPIRIT point 32*), (Additional file 3), they hand each participant an envelope with the stigma questionnaire—to be self-administered. Fieldworkers either wait for a respondent to fill in the questionnaire, or arrange a time and place to collect the completed questionnaire from the respondent if it is not convenient for the respondent to fill it in immediately. Respondents with low levels of reading literacy are gathered into small groups, the fieldworkers work through the questions verbally *with the whole group*, and address any queries with the whole group; however, respondents have to fill in the questionnaires themselves.

When the respondent hands in their completed questionnaire, the fieldworker quickly scans through each one to check for completion (not to see the person’s actual answers). Where substantial sections of the questionnaire are not completed, the fieldworker marks the places and hands it back to the respondent to complete properly. This helps to ensure that the dataset is not overly compromised by being incomplete.

As described in the ‘Ethics’ section, respondents’ names are replaced with a unique number that is pasted onto their consent forms, their completed survey questionnaires, and the participant list kept by the fieldworkers. Each day, the lists, consent forms, and completed questionnaires are handed to fieldwork team leaders, who are responsible for collating information at the end of each day (i.e. how many respondents are reached, number of questionnaires completed/outstanding, and highlighting which respondents still need to be reached). The fieldwork teams maintain telephone contact with the CHSR&D on a daily basis and once a week they meet face-to-face with one of the project principal investigators (PIs). The purpose of this meeting is to report back on progress, any difficulties experienced, and hand in completed questionnaires.

The baseline questionnaires included the stigma scales from the Stigma Score Pilot Study (HIV stigma among HCWs; TB stigma among HCWs); the validation of these scales was published in *Clinical Infectious Diseases* [21]. Three new scales were added (General climate of *HIV* stigma in the hospital; General climate of *TB* stigma in the hospital; HIV and TB stigma combined). The baseline stigma scales are provided in the appendices (Additional file 5); (SPIRIT point 18a).

There were also several other sections collecting data on important stigma-related issues (demographics; basic and advanced HIV and TB knowledge; HIV and TB infection control in the workplace; confidentiality in the workplace; HIV status disclosure in the workplace; testing and treating for HIV and TB; and knowing people with HIV and TB). The full baseline instrument is available from the corresponding author on reasonable request.

### Post-intervention data collection

The same processes and protocols are followed for the post-intervention survey. Respondents from the baseline survey are tracked down via their unique identifiers and asked to complete the post-intervention questionnaire. As noted before, there was a 50% oversampling of respondents to allow for loss-to-follow up between baseline and post-intervention surveys (SPIRIT point 18b).

To ensure comparability, the post-intervention survey will resemble the pre-intervention survey, thus including the HIV/AIDS and TB stigma scales as well as the range of other key outcome measures related to stigma at the individual, community, and structural levels—as described above. The post-intervention survey will also have a new section to measure the reach and appeal of the stigma interventions.

### Qualitative data collection

Qualitative data are collected at several junctures during the trial. Data collection always complies with informed consent and protocols discussed later, in the ‘Ethics’ section.

As agreed in the Memorandum of Agreement (MoU) between FSDoH and CHSR&D, mid-way through the interventions an outside assessor recruited by the FSDoH collects data on the trial interventions and trial conduct from purposively selected individuals.

Following the change-agent training sessions, approximately 10 focus group discussions comprising 8–10 people each are held with purposively selected HCW change agents who attended the training. All sessions will be audio-recorded. The aim of is to see *if* and *how* the change agents mobilised the knowledge of HIV and TB stigma that they gained from the training workshops and how, if at all, they were able to use some of the stigma-reduction communication techniques they learned.

Audio-recorded focus group discussions may also be held with purposively selected HCWs at all levels who did *not* attend the change-agent training. The broad aim is to explore their perceptions of HIV and TB stigma and if and how it manifests in the workplace. It will also be interesting to probe their awareness and reception of the social marketing campaign and its effects.

Qualitative data are also collected by CHSR&D researcher team members via one-on-one in-depth interviews, audio-recorded, with any HCWs who are/were infected with HIV and/or TB and who are willing to share their experiences of stigma and support in the workplace.

### Data processing and management (SPIRIT point 19)

#### Baseline data processing and management

The CHSR&D has a dedicated, secure data processing room, as well as a dedicated secure data storage room. All UFS computers are password protected; in addition project data files are encrypted.

A quarter of the collected questionnaires are randomly selected for purposes of developing a coding list for open-ended questions. Four data coders collaboratively develop the coding list. To ensure quality and accuracy, data are double-captured and cleaned in SPSS. Frequency counts are calculated for all questions to check for outliers. The two datasets are then checked for any discrepancies and corrected.

As noted in the ‘Ethics’ section below, no respondent names appear in the SPSS database, only their unique identifying numbers. The list with the names of participants will be kept separate from the database, and will only be used for the post-intervention survey, when we need to know who to follow-up. All research data and documents referring to the trial will be stored and maintained in a secured storage space at the CHSR&D, UFS, for a minimum of 10 years from the end of the trial.

#### Post-intervention data processing and management

The same processes and protocols are followed for the data gathered from HCWs’ evaluation of training interventions, as well as for the post-intervention survey.

#### Qualitative data processing and management

Each focus group discussion is audio-recorded using two digital recording devices, and notes are taken by a research assistant. Audio-recordings and notes are transcribed verbatim into Microsoft Word by an independent commercial company. A member of the research team reads through the interview data to address spelling mistakes, inconsistent spacing and formatting, and to check for and resolve any possible transcription errors. Cleaned transcriptions are then imported into NVivo version 11 for the electronic management of analyses. The dataset will be digitally secured with a password, shared only among the members of the analysis team.

One-on-one in-depth interviews are also recorded on a digital recording device. Audio-recordings are transcribed verbatim to Microsoft Word by a research officer at the CHSR&D. A member of the research team will read through the interview data to address spelling mistakes, inconsistent spacing and formatting, and to check for and resolve any possible transcription errors. Any information that identifies a particular hospital, person, or participant will be replaced by unique identifying numbers. Transcribed data are then imported into to NVivo version 11 for the electronic management of analyses. The dataset will be digitally secured with a password, shared only among analysis team members.

